### Statistical Analysis

The primary analysis will use the N-of-1 trials to obtain individual and population-level estimates of the efficacy of cerebellar DBS in ameliorating movement disorder symptoms and in improving QOL for children and young adults with DCP. We will use an intention-to-treat analysis. We anticipate that, within each participant, within-arm CPCHILD and MD-CRS 4–18-R scores measuring the effects of cerebellar stimulation will be relatively stable over time, with slopes approximately parallel with some possible carryover from the effective to sham stimulation arm, based on our prior experience with cerebellar DBS(24). Based on weekly assessments, each participant will contribute 4 values per arm per block. Within each block, we will treat the participant’s arm-specific values as simultaneous replicates and attribute them to the midpoint of the relevant follow-up interval.

To accommodate alternatives to Gaussian distributions of the measured outcomes, we will analyze them using a generalized linear mixed model (GLMM), with treatment arm, and follow-up time as fixed effects and the subject as a random effect. With 3 blocks per arm, an arm-by-time interaction is unlikely to be needed but will be evaluated in a sensitivity analysis; we will also consider a simplification of the model that substitutes blocks for time. Output of the model will include estimates of the participant-specific mean (95% confidence interval) difference between arms, as well as the overall mean difference (95% confidence interval) between arms and overall plot. An interim analysis of the success of cerebellar stimulation will be performed after the first set of 2 subjects is studied.

The N-of-1 trial design is particularly useful when treatment effects exhibit variability between individuals (38), as is the case for DBS for complex movement disorders in DCP(10). N-of-1 designs provide the most rigorous evidence for treatment decisions at the individual level. In addition, when outcomes are aggregated from several patients, N-of-1 trials can yield treatment effect estimates applicable to the broader population, and close to the level of evidence of randomized controlled trials (39). While not previously used in DBS for dystonia, the N-of-1 design was found to be useful for assessing DBS efficacy in neuropathic pain (40), and it has been more recently recommended for uncommon movement disorders (41).

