An assumption for N-of-1 trials is that the treatment to be assessed should have relatively rapid onset and washout, with limited carryover effects. While the beneficial effects of DBS in dystonia following pallidal stimulation may manifest after a delay, non-invasive cerebellar transcranial magnetic stimulation (TMS) and transcranial direct current stimulation (tDCS), and cerebellar DBS appears to have a fast onset and quick wash-out of benefit(24). If significant delayed-onset and carry-over are observed (during interim analyses), the blinded assessments at the 12-month visit (compared to pre-stimulation baseline) will be used as an endpoint for efficacy. If participants do not tolerate sham or effective stimulation due to resurfacing of dystonia/choreoathetosis, spasticity, and/or pain, we will shorten each block duration by two-to-three weeks. If this is not tolerated, we will continue effective (or sham) stimulation and analyze data for that participant both as intention-to-treat and on an ‘as treated’ basis. The percentage of participants who successfully identify their stimulation settings (effective vs. sham) and are unable to tolerate sham or effective settings will be considered a surrogate secondary endpoint for preliminary effectiveness. In that instance, the effects of the open-label intervention on the blinded video motor ratings and QOL at five months (before the randomized phase) and at 12 months, will be compared to the preoperative baseline.

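### The endpoint switch depends on seeing delayed onset and carry-over, but the stated model drops weekly timing and previous condition and so would not show them

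*Protocol article*

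**What the plan says.** All of this stands in the Statistical Analysis section of the protocol article.

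- **Trigger.** "If significant delayed-onset and carry-over are observed (during interim analyses), the blinded assessments at the 12-month visit", compared with the pre-stimulation baseline, become the efficacy endpoint.
- **Data.** With weekly assessments, "each participant will contribute 4 values per arm per block". Three blocks and two arms make 24 values per participant.
- **Coding.** Within each block the plan treats the "arm-specific values as simultaneous replicates and attribute them to the midpoint of the relevant follow-up interval".
- **Model.** A generalized linear mixed model "with treatment arm, and follow-up time as fixed effects and the subject as a random effect".
- **Time pattern.** The plan says that "an arm-by-time interaction is unlikely to be needed but will be evaluated in a sensitivity analysis". As an alternative, "we will also consider a simplification of the model that substitutes blocks for time", which is coarser still.
- **Interim.** The only look described is this: "An interim analysis of the success of cerebellar stimulation will be performed after the first set of 2 subjects is studied".

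The same section expects some carry-over from effective to sham stimulation. The Sample Size section assumes it is minimal.

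**The concern.** Slow onset and slow wash-out leave two traces: a trend over the weeks after a switch, and a difference between months that follow the other condition and months that follow the same one. The stated model keeps neither. The weekly trend goes into residual error because all four values share one time point, and the previous condition is not in the model.

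Rapid onset and wash-out is the assumption that the article itself names for this design. If it fails, the effective-versus-sham difference shrinks, and nothing in the stated model signals this. The diluted figure would be reported as the effect, and the rule for changing the endpoint would have no stated analysis to inform it.

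**Working it through.** The plan gives no figure on this point to reproduce. From the documents I take the 10-point difference, n = 10, the interaction SD of 12.6, the eight sequences with five participants starting on each arm, and an effective open-label phase before month 1. The weekly rates and the other SDs are assumptions.

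**1. Design rows.** 10 participants × 6 months × 4 weeks = 240 records. Under midpoint coding they fall on 10 × 6 = 60 distinct design rows, so within-month build-up or decay has no regressor.

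**2. What each month follows** (eight sequences, equal weight, effective lead-in):

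| | Block 1 | Block 2 | Block 3 |
|---|---|---|---|
| Sham months that follow effective | 100% | 75% | 75% |
| Effective months that follow sham | 50% | 75% | 75% |
| Sum of the two shares | 1.5 | 1.5 | 1.5 |

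On average 1.5 of 6 months per participant (about 15 of 60) follow the same condition.

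**3. Dilution when both are equally slow.** Suppose a share k of the remaining distance is covered each week. The mean shortfall in a month after a switch is L = [(1−k) + (1−k)² + (1−k)³ + (1−k)⁴]/4.

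- k = 0.5: L = 0.9375/4 = 0.234. Block difference = 10 × (1 − 1.5 × 0.234) = 6.48.
- k = 0.3: L = 1.7731/4 = 0.443. Block difference = 10 × (1 − 1.5 × 0.443) = 3.35.

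This treats each month as starting from the full level of the previous condition. If the state instead carries on continuously from month to month, enumeration gives 6.56 and 3.88. In every case the figure is the same in all three blocks, so the expected arm-by-block interaction is zero although a third to two-thirds of the effect is lost.

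On month midpoints instead of blocks, a noise-free least-squares fit of arm, time, their product and participant to the eight sequences gives a small interaction: −0.17 points per month (k = 0.5) and −0.26 (k = 0.3). That would look like a slowly fading effect, not a lag after switching.

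**4. Carry-over alone (k = 0.3, immediate onset).** Block 1: 10 × (1 − 1.00 × 0.443) = 5.57. Blocks 2 and 3: 10 × (1 − 0.75 × 0.443) = 6.68. Here the interaction is not zero, but it is small.

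**5. Rejection rates at 0.05, 10 participants, by simulation.** Two sets of assumptions were used: weekly SD 8; or weekly SD 5 with month SD 3 and block SD 3, and interaction SD 0 or 12.6. The models were least-squares approximations to the stated one.

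| Term | Both slow | One effect only |
|---|---|---|
| Arm-by-time | about 4-7% | 4-13% |
| Condition by weeks since switch | about 43-98% | about 33-63% (carry-over alone) |
| Previous condition | about 35-60% (weekly SD 8) | about 8-20% (carry-over alone) |

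**6. Two participants, as at the interim look.** With weekly SD 8 and both slow, an arm-by-week term and a previous-condition term reject in 9-17%. With weekly SD 5 and carry-over alone, the weeks-since-switch term rejects in about 12-15% and the previous-condition term in 8-9%. My own run with weekly SD 5 and both slow (600 trials per setting) gave about a third for weeks since switch.

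**The case against.** The strongest reply is that the article never assigns arm-by-time the job of checking onset or wash-out. It appears as a possible refinement of the efficacy model, and the article leaves the method of the interim judgement unnamed. Midpoint coding is fixed only for that model and deletes no data. A full analysis plan, not shown here, could use the weekly scores. That is right as far as it goes. A reader might infer that the authors would take a null arm-by-time result as proof of quick wash-out, but the text does not say so. A reader might also infer that the trial cannot detect carry-over at all; the weekly data could show it. What remains is a stated coding and a stated list of terms that remove the information a stated decision rule needs. That is a mismatch within one section, not detail left to another document.

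Three further limits stand.

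- The trigger joins delayed onset and carry-over with "and", so it should not be read as requiring only one. Both together is also the case in which arm-by-time is least informative.
- A zero expected interaction holds block by block when onset and wash-out are equally slow. The article expects fast onset with some carry-over, and there arm-by-time has a little power: 5-7% with the smaller SDs. Its highest rate with any single effect was 13%.
- Better terms do not rescue the interim decision, as step 6 shows.

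**Conclusion.** The point holds for the analysis that the article states. That model has no regressor for within-month build-up or decay and no term for the previous condition, and its one time-pattern term answers a different question. A true 10-point difference could be reported as about 6.5 (50% per week) or about 3.9 (30% per week; 3.35 if each month starts from the full previous level), with no sign of the violation.

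The transition shares and the equal block differences are exact enumeration and need no SD. The sizes depend on the assumed weekly rates, and the rejection rates also on the assumed SDs; the documents give neither. If onset and wash-out are as fast as the article expects, the dilution is small and the cost of the omission is mainly that nobody could show it. This should be corrected before the data are analysed; it does not invalidate the design.

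**What to change.** Keep the actual week of each assessment, and pre-specify on all 10 participants:

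1. **Main check:** a condition-by-weeks-since-switch term, fitted in months that follow a change of condition.
2. **Supporting check:** a previous-condition term. The months that follow the same condition (about 15 of 60, counting the open-label lead-in) serve as the reference least exposed to carry-over.
3. **Reporting:** both estimates with confidence intervals. Keep arm-by-time only as a check on drift of the effect.

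Also state three limits: power is moderate (about 33-63% for carry-over alone, lower for the previous-condition term); a non-significant result does not confirm absence of carry-over; and the two-participant interim look cannot support the decision to change the endpoint, so say when and by what criterion that decision is made.

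The cost is plan wording and a little more analysis. The weekly data are already collected, and no visit or procedure changes.

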#### Study Design and Setting

This is a single-center series of randomized, double-blinded N-of-1 trials to test the effects of chronic DBS of dentate and cerebellar output pathways on severe movement and tone disorders in DCP. This study will recruit ten children and young adults aged 7–25 with DCP secondary to hypoxic ischemic static encephalopathy (HIE). We will implant Medtronic Percept^™^, an FDA-approved “bidirectional” neurostimulator that can sense and store brain activity while delivering DBS therapy.

We will use a series of N-of-1 clinical trials to enhance causal inference and mitigate the variability in clinical features in this population (Fig. 1). We will use a cross-over design and compare three months of effective stimulation with three months of sham stimulation for each patient. We will administer the trea^™^ents in blocks of two months with one month per condition (sham vs. effective stimulation) in a randomized order. During these one-month trials for each condition, patients, caregivers, and assessing clinicians will be blinded to the state of the stimulator, and outcomes will be measured at weekly intervals. To evaluate kinematic metrics, we will use videotaped automated movement recognition techniques and formal gait analysis.

This protocol was developed to adhere to the Standard Protocol Items: Recommendations for Interventional Trials (SPIRIT) extension for N-of-1 trials (SPENT) checklist that is aligned with the CONSORT (consolidated reporting items for trials) extension for N-of-1 trials (CENT, 29).

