#### Phase 4: Subsequent follow-up

After the three N-of-1 blocks, the last clinic visit of the study will include repeated neuropsychological testing, QOL and pain questionnaires, videotaped motor assessments, brain recordings, and a second brain MRI. After the conclusion of the study, and for five years following DBS surgery, participants will be invited to return yearly for a research visit for DBS checks and detailed assessments of neurological and behavioral function.

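### If an interim look suggests carry-over, an uncontrolled 12-month-versus-baseline comparison becomes an efficacy endpoint, and nothing says the randomised sham contrast stays primary

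*Protocol article*

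**What the plan says.** Study Design and Setting describes a within-patient crossover that will "compare three months of effective stimulation with three months of sham stimulation for each patient". The Statistical Analysis section builds the main efficacy result on it: "The primary analysis will use the N-of-1 trials to obtain individual and population-level estimates of the efficacy of cerebellar DBS", by intention to treat, in a generalised linear mixed model with treatment arm and follow-up time as fixed effects.

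The same section schedules one early look: "An interim analysis of the success of cerebellar stimulation will be performed after the first set of 2 subjects is studied". It then gives a contingency. The condition is "If significant delayed-onset and carry-over are observed (during interim analyses"), and the consequence is that "the blinded assessments at the 12-month visit (compared to pre-stimulation baseline) will be used as an endpoint for efficacy".

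Carry-over is not treated as remote. The section expects stable scores within each arm "with some possible carryover from the effective to sham stimulation arm", whereas the Sample Size section assumes it to be minimal.

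A second set of baseline comparisons, covering "the effects of the open-label intervention on the blinded video motor ratings and QOL at five months" and at 12 months, belongs to a separate contingency for participants who cannot tolerate a setting. It is not part of this point.

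**The concern.** The randomised sham comparison is the one element of this design that can attribute a change to stimulation. The contingency brings in an efficacy endpoint with only the patient's own pre-stimulation state as reference. Any change over the year then counts towards efficacy: expectation after brain surgery, regression to the mean after enrolment at a bad time, development in children and young adults, and other care.

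The contingency applies exactly when the crossover assumption is judged to have failed. The text neither keeps the randomised contrast as primary nor limits what may be concluded from the baseline comparison. If the rule were followed as most readers would take it, the trial could report efficacy from an uncontrolled comparison while still being described as a randomised, double-blind series.

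Calling the 12-month assessments blinded helps only in part. The one measure described for hiding time since surgery is the cap worn in videotaped motor assessments (Phase 3). CPCHILD, the primary quality-of-life outcome, is a caregiver report (Table 1), and caregivers know whether surgery has taken place. A before-after CPCHILD comparison would therefore not be masked.

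**Working it through.** The plan gives no figure for this contingency, so there is none to reproduce. The calculations below show the size of the problem under stated assumptions.

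**Inputs from the protocol article**
- n = 10 and two-sided alpha 0.05 (Sample Size).
- A 10-point CPCHILD difference is clinically relevant (Sample Size).
- SD 12.6 (Sample Size). It is given there as a treatment-by-patient interaction SD; its use as a before-after SD is an assumption.
- Interim after 2 participants; 4 weekly values per arm per block (Statistical Analysis). With 3 blocks this makes 3 sham months per participant, so 6 in all.

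**Assumptions not in the documents**
- Non-specific improvement b of 0, 5 or 10 points.
- Before-after SD s of 8, 12.6 or 16.
- Weekly SD of 3 to 10 for the carry-over check.

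**1. Before-after test when stimulation does nothing**

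This is conditional on the switch having been made. The test is a one-sample t on 10 changes, df 9, critical value 2.262. Its noncentrality is b / (s/√10).

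| b | s = 8 | s = 12.6 | s = 16 |
|---|---|---|---|
| 0 | 5% | 5% | 5% |
| 5 | 5/2.530 = 1.98 → 42% | 5/3.984 = 1.25 → 20% | 5/5.060 = 0.99 → 14% |
| 10 | 10/2.530 = 3.95 → 94% | 10/3.984 = 2.51 → 61% | 10/5.060 = 1.98 → 42% |

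In the randomised contrast, a shift common to the effective and sham months cancels and the error rate stays at 5%. The excess in the table comes entirely from b, that is, from having no control.

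**2. What two participants can show about carry-over**

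Take week 1 minus week 4 of each sham month as a simple measure of residual effect. There are 6 values, each with SD (weekly SD × √2), tested by a one-sample t with df 5 and critical value 2.571. For a residual of c points the noncentrality is c / (weekly SD × √2/√6).

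| Weekly SD | c = 5 | c = 10 |
|---|---|---|
| 3 | 2.89 → 64% | 5.77 → 99% |
| 5 | 1.73 → 29% | 3.46 → 79% |
| 7 | 1.24 → 17% | 2.47 → 51% |
| 10 | 0.87 → 11% | 1.73 → 29% |

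A 5-point residual, half the clinically relevant difference, is found in 11% to 64% of cases. This measure ignores weeks 2 and 3 and the effective months. It also counts all six sham months, although sequences containing AB-BA (Phase 3) place one sham month directly after another. The result is a rough guide: two participants are a weak basis, not a worthless one.

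**The case against.** **Replacement is not stated.** The text says an endpoint for efficacy, not the primary endpoint, and the statement that the N-of-1 trials supply the primary analysis is never withdrawn. This stands. A reader might infer that the randomised comparison is discarded; the document does not say so. What remains is that it does not say the opposite, in the one situation where it matters.

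**The 20% and 61% are conditional.** If stimulation truly does nothing, there is nothing to carry over and the switch occurs only by mistake. With a 5% false-trigger rate, and the two steps treated as independent, the joint rate is 0.05 × 0.20 = 1% to 0.05 × 0.61 = 3%. That is a fair correction for a formal trigger. The article gives no criterion, and under a judgement-based trigger a null sham contrast could itself be read as carry-over. The figures should therefore be read only as the error rate once the switch has been made.

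**It is not an interim-analysis error.** A reader might infer that seeing outcome data inflates type I error, or that the interim uses unblinded data. Neither is supported. The contingency is written in advance, the same test gives 5% with no drift, and the article does not say who sees the interim data or in what form.

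**The blinded assessments may be the videos only.** That is possible, and the motor ratings could then be masked to time since surgery. Masked ratings would still have no sham comparator.

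**Other stronger readings.** With two participants the 95% CI half-width for the treatment effect is 12.71 × 12.6/√2 = 113 points, but that concerns the treatment effect, not carry-over. The schedule adds up to 1 + 4 + 6 = 11 months, which does not conflict with a 12-month visit: Phase 4 places it last ("After the three N-of-1 blocks, the last clinic visit of the study will include repeated neuropsychological testing"). The stimulation setting at that visit, the trigger threshold and the decision-maker are details an article may leave to the full protocol or analysis plan.

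**Feasibility and safety are called the primary objectives** later in the Statistical Analysis section. That lowers the stakes, but Study Outcomes and the planned analysis still promise efficacy conclusions.

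**Conclusion.** The point holds as a should-fix. The article states a rule under which a comparison without sham or concurrent control serves as an efficacy endpoint, and it neither secures the primacy of the randomised contrast nor limits the resulting claim. That replacement follows is the natural reading but an inference.

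The size depends on assumptions that the documents do not supply. Once the switch has been made, and with no true effect, a 5-point non-specific improvement gives a significant result in 20% of trials (14% to 42% for SDs of 16 to 8). A 10-point improvement gives one in 61% (42% to 94%). Evidence for carry-over from two participants is weak unless weekly scores are very stable or the residual effect is large.

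**What to change.** Change the Statistical Analysis text in three places:

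1. State that the randomised effective-versus-sham contrast remains the primary efficacy analysis whatever the interim shows.
2. Handle carry-over and delayed onset inside that analysis by a rule fixed beforehand and based on the weekly scores. Examples are using only the later weeks of each period, or adding a term for the preceding condition.
3. Label the 12-month-versus-baseline comparison supportive and uncontrolled.

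An efficacy look after two participants need not be dropped; it should simply not decide which comparison carries the efficacy claim.

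The cost is wording. Visits and data collection are unchanged. The fallback efficacy claim is given up, and a late-week window loses a little precision. For example, if weekly errors are independent, using 3 of the 4 weeks raises the within-period standard error by √(4/3) = 1.15 and leaves the between-patient variation in effect untouched.

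### The surrogate effectiveness endpoint counts intolerance of effective stimulation in the same way as intolerance of sham, so it has no direction

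*Protocol article*

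**What the plan says.** The text is in the Statistical Analysis section of the protocol article, in the paragraph on onset, washout and tolerability.

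- **Trigger.** The paragraph covers intolerance of either condition: "If participants do not tolerate sham or effective stimulation due to resurfacing of dystonia/choreoathetosis, spasticity, and/or pain".
- **First step.** In that case "we will shorten each block duration by two-to-three weeks".
- **Second step.** If that also fails, the participant stays on effective (or sham) stimulation, and the plan is to "analyze data for that participant both as intention-to-treat and on an" as-treated basis. The general rule earlier in the section is "We will use an intention-to-treat analysis".
- **Endpoint.** The share of participants who recognise which condition they are on and "are unable to tolerate sham or effective settings will be considered a surrogate secondary endpoint for preliminary effectiveness".
- **Companion analysis.** In the same situation, blinded video ratings and quality of life at five and 12 months are compared with the preoperative baseline.

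The endpoint is not in the list of key secondary outcomes under Study Outcomes.

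**The concern.** An effectiveness endpoint should rise when treatment helps and fall when it fails. This one puts two opposite events into one numerator. Symptoms that return when stimulation is reduced to sham support benefit. Symptoms that return on the participant's best effective setting are treatment failure. Both add one to the count.

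The endpoint is meant for the case in which the randomised comparison is compromised because participants cannot stay on an assigned setting. In a 10-participant trial of an experimental implant in children and young adults, it could then be one of the few figures quoted as a sign of benefit. A high value could come from a device that works, from one that does nothing, or from one that participants cannot bear.

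**Working it through.** The plan attaches no expected value or success threshold to this endpoint, so there is no planned figure to reproduce. The check asks how the definition behaves.

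**Inputs from the protocol article**
- n = 10 (Sample Size).
- A participant counts if the setting is identified *and* sham *or* effective stimulation is not tolerated (Statistical Analysis).
- Intolerance of either setting means resurfacing symptoms (Statistical Analysis).

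**Assumptions, none of them in the document**
- qS and qE are the probabilities of not tolerating sham and effective stimulation.
- g is the probability of correct identification.
- The three events are independent.

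**Formula**

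Expected score = g × [1 − (1 − qS)(1 − qE)]

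**1. Symmetry.** Exchanging qS and qE leaves the score unchanged. Take g = 1:
- Sham tolerated worse (qS = 40%, qE = 10%): 1 − 0.6 × 0.9 = 46%.
- Effective stimulation tolerated worse (qS = 10%, qE = 40%): 1 − 0.9 × 0.6 = 46%.

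The endpoint gives both trials the same result. The difference qS − qE separates them: +30 and −30 percentage points.

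**2. Extreme case.** If all 10 participants identify effective stimulation and none tolerates it, the score is 10/10 = 100%.

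**3. Inert device.** Set qS = qE = q and g = 0.5, a single two-option guess.

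| q per condition | intolerant of either, 1 − (1 − q)² | expected score, × 0.5 | qS − qE |
|---|---|---|---|
| 10% | 19% | 9.5% | 0 |
| 20% | 36% | 18% | 0 |
| 30% | 51% | 25.5% | 0 |
| 50% | 75% | 37.5% | 0 |

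**4. Does the identification requirement help?** Only if participants identify the setting solely from symptom benefit. The document gives three other routes or leaves them open:
- Chance alone gives g = 0.5.
- Blinding begins only after an open-label phase with several months of programming (Phase 2 and Phase 3), so families already know what active stimulation is like.
- The paragraphs on risk at the end of Statistical Analysis list ataxia, hypotonia and dysarthria as possible stimulation effects.

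For a device with no symptomatic benefit that is always recognised, g = 1. At q = 20% the score then rises from 18% to 36%. Better recognition raises the score without any benefit.

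**5. What a directional test can show at n = 10.** In an exact two-sided sign test on participants who tolerate one condition but not the other, five of five in one direction gives 2 × 0.5⁵ = 0.0625, and six of six gives 2 × 0.5⁶ = 0.031. At least six discordant participants are needed to fall below 0.05, so the comparison is essentially descriptive.

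**The case against.** The best defence is that the authors meant symptom return on sham. Intolerance is framed as resurfacing of symptoms rather than as side effects. A participant whose symptoms return on effective stimulation might well guess sham and so fail the identification condition. The measure is also labelled surrogate, secondary and preliminary, it sits outside the key secondary list, and it is accompanied by blinded ratings against baseline. No primary conclusion rests on it.

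The point about limited reach stands. The point about intent is plausible, but the wording does not carry it. The section foresees intolerance of effective stimulation in the trigger, in the continuation rule and again in the endpoint, so the words are not a stray slip. The identification condition removes such participants only if they guess from symptoms alone.

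Two stronger readings are tempting, and the document does not support either.

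- **That a correct guess by itself counts as success.** It does not. The two conditions are joined by *and*, so guessing without intolerance scores nothing. For the same reason, the 100% case needs every intolerant participant also to have identified the setting.
- **That intention-to-treat is the wrong analysis because later sham periods may hold effective-stimulation scores.** The pull towards zero is real if stimulation works, and it also occurs when a participant stays on sham. But intention-to-treat is a defensible choice, blocks are shortened before anyone leaves the alternation, and an as-treated analysis is already planned for these participants. The size depends on an escape rate that the document does not give. With the planned 10-point effect and two average participants of 10 escaping, the contrast becomes 10 × (1 − 0.2) = 8.0 if they lose it entirely, or 10 × (1 − 0.2 × 2/3) = 8.7 if they lose blocks 2 and 3 only. It would be lower if the strongest responders escaped. Replacing intention-to-treat with a missing-at-random analysis, or dropping the as-treated one, is a preference about the estimand on which statisticians differ.

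**Conclusion.** The endpoint is wrongly defined as written. It is unchanged when the results on sham and effective stimulation are exchanged, so it cannot be read as effectiveness. It can reach 100% with a treatment that nobody tolerates. For an inert device its expected value is 9.5% to 37.5% as assumed intolerance runs from 10% to 50% per condition, with 50% guessing and independence. The percentages rest on those assumptions; the lack of direction follows from the definition alone. The consequence is confined to a fallback secondary measure, but in the situation it is meant for it could mislead. The finding does not extend to the choice of intention-to-treat for the primary analysis.

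**What to change.** 1. Replace the single percentage with two: participants unable to tolerate sham, and participants unable to tolerate effective stimulation. Give each with its denominator and the number of blinded periods started on that condition.
2. Base any effectiveness reading on the within-participant comparison of intolerance during sham with intolerance during effective stimulation, using an exact sign (McNemar) test on discordant participants. Label it descriptive at n = 10.
3. State that intolerance of effective stimulation is evidence against benefit, and report it under safety and tolerability.
4. Report correct identification separately as a blinding check, outside any effectiveness endpoint.
5. Keep the planned intention-to-treat and as-treated analyses. Where participants leave the alternation, report how many did so and in which direction, and note that intention-to-treat then pulls the contrast towards zero.

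**Cost.** This is a change of wording in the protocol or analysis plan. The present definition already requires tolerance and identification to be recorded, so no new data are needed. The price is a less striking summary figure and a test with little power. No change to block length or to the rules for leaving a condition is proposed.
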